### Statistical analysis and sample size

It is hypothesized that nivolumab and ipilimumab will increase overall survival. It is assumed that an immunotherapy approach consisting of a nivolumab monotherapy in conjunction with a safety guided treatment escalation to a nivolumab/ipilimumab combination regimen increases the 1-year overall survival rate by a margin of 13% compared to historical control for standard chemotherapy (i.e. nivolumab monotherapy followed by a conditional nivolumab + ipilimumab therapy 1-yr-OS = 30% vs CTx-control 1-yr-OS = 17%) [4]. Based on these assumptions, and an exponential shape of the survival curve, a one-sided, one-sample log rank test calculated from a sample of 69 subjects achieves 90.3% power at an alpha = 0.05 one-sided significance level to detect a proportion surviving of 0.3 in the experimental group when the proportion surviving in the historic control group is 0.17. These proportions surviving are for a period of 12 month (1-year-OS rate). Subjects are accrued for a period of 12 month. Follow-up continues for a period of 24 month after the last subject is added. The probability that a subject experiences an event during the study is 0.9477. The expected number of events during the study is 65. To compensate for uninformative drop-outs a total of *N* = 75 subjects need to be recruited. All patients, both on monotherapy and on combination therapy, are subject to statistical ITT analysis.

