## Background

ESCC is the sixth leading cause of cancer-related death worldwide [1]. The disease is frequently diagnosed in advanced tumor stages and in elderly patients [1, 2].

Efficacy of chemotherapy in advanced ESCC is still poorly defined. While most patients undergo chemotherapy and/or chemo-radiation in first line according to the CROSS protocol using Paclitaxel and Carboplatin, effectiveness of second-line chemotherapy is discouraging [3, 4]. However, very recently Kojima et al. reported that pembrolizumab significantly improved OS compared to chemotherapy (paclitaxel, docetaxel or irinotecan) in patients with advanced esophageal or esophagogastric junction carcinoma whose tumors express PD-L1 (Combined Positive Score [CPS] ≥10, regardless of histology) (median 9.3 vs 6.7 mo; HR 0.69; 95% CI 0.52–0.93; *P* = 0.0074). OS at 12 months was 43% vs 20%, respectively. (KEYNOTE 181) [5].

Immunotherapy with antibodies against immune checkpoints like PD-1/PD-L1 represents a new treatment opportunity with relatively little side effects and first promising results in the treatment of squamous cell carcinoma patients [6–8]. With respect to esophageal cancer, preliminary results from an Asian study indicate efficacy of nivolumab [9]. From 64 heavily pre-treated patients, 11 (17, 95% CI 10–28) had an objective response and 16 (25, 95% CI 16–37) demonstrated stable disease. The median overall survival was 10.8 months (IQR 4.9–14.3) in this trial population (unselected for PD-L1 expression status). Long-term survival was also improved by pembrolizumab as described by Doi et al. [10].

Furthermore, the CheckMate 012 trial demonstrated that overall response rates could be doubled when PD-1 inhibitor nivolumab was combined with CTLA-4-inhibitor ipilimumab in advanced NSCLC patients [11]. In this trial, grade 3 and 4 adverse events were reported to occur in 33% of the patients treated with the combination therapy (nivolumab 3 mg/kg Q2W and ipilimumab 1 mg/kg Q6W). In the checkmate 032 in turn (nivolumab 3 mg/kg Q2W and ipilimumab 1 mg/kg Q3W), treatment related adverse events of grade 3 and 4 were only slightly enhanced when compared to nivolumab monotherapy (13% vs. 19%) [12].

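### The only null curve stated for the primary one-sample log-rank test, an exponential through 17% at 12 months (median 4.7 months), conflicts with the protocol's own historical survival figures, so the 5% error rate is not secured.

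*Protocol article*

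**What the plan says.** All design figures are in the protocol article, section Statistical analysis and sample size.

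- The effect is expressed as 1-year survival rates: "1-yr-OS = 30% vs CTx-control 1-yr-OS = 17" (per cent). The section adds: "These proportions surviving are for a period of 12 month (1-year-OS rate".
- The test and shape are "an exponential shape of the survival curve, a one-sided, one-sample log rank test", "calculated from a sample of 69 subjects", which "achieves 90.3% power at an alpha = 0.05 one-sided significance level".
- Accrual lasts 12 months. "Follow-up continues for a period of 24 month after the last subject is added", so each patient can be observed for 24 to 36 months.
- The stated event probability is 0.9477, with 65 expected events.

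Two other places give historical survival on second-line chemotherapy. The Discussion, citing the same source as the 17%, describes overall survival as mostly confined to 6 to 8 months. The Background reports a randomised trial whose chemotherapy arm had a median of 6.7 months, and says "OS at 12 months was 43% vs 20%, respectively", the second figure being chemotherapy.

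**The concern.** A one-sample log-rank test compares observed deaths with the deaths expected if every patient followed the reference curve for as long as that patient was observed. It therefore needs a null cumulative hazard at all times, not only at 12 months. The protocol supplies one point and a shape, which together give a constant hazard from entry to month 36.

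In a single-arm trial the reference curve is the comparator. If real chemotherapy patients die more slowly than this curve in the first months and faster later, the curve expects too many deaths over the time they are observed. The test can then reject although 12-month survival has not improved at all. The protocol's own figures suggest such a mismatch.

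**Working it through.** **1. Reproduce the plan.** Inputs: 12-month survival 0.17 and 0.30, exponential, 69 patients, accrual 12 months, further follow-up 24 months, one-sided 5%.

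- Hazards: h0 = −ln(0.17)/12 = 0.1477 and h1 = −ln(0.30)/12 = 0.1003 per month; ratio 0.679.
- Event probability under the alternative: p = 1 − [exp(−24·h1) − exp(−36·h1)]/(12·h1) = 0.9477. Expected events: 69 × 0.9477 = 65.4.
- Null-expected deaths per patient under the alternative: e = p/0.679 = 1.395. The standard deviation of (observed − expected) per patient is 1.361.
- Power of Z = (O − E)/√E: Φ[(−1.645·√1.395 + √69·(1.395 − 0.948))/1.361] = 90.3%.

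All three stated figures reproduce, so the exponential through 17% is the null on which the 90.3% rests.

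**2. Compare that null with the quoted history.**

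- Null median: ln 2/0.1477 = 4.7 months, against 6 to 8 months in the Discussion.
- An exponential with median 6 or 8 months would have 0.5^(12/6) = 25% or 0.5^(12/8) = 35% alive at 12 months, not 17%.
- Background chemotherapy arm: an exponential with median 6.7 months gives 0.5^(12/6.7) = 29% at 12 months; 20% is reported. The Weibull through both points has shape k = ln(ln 5/ln 2)/ln(12/6.7) = 1.45.

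**3. Type I error when only the shape is wrong.** True 12-month survival is held at exactly 17%, n = 69, with the planned accrual and follow-up, no drop-out, and the reference curve exponential through 17%. For a Weibull curve through 17% with median m, k = ln(ln(1/0.17)/ln 2)/ln(12/m). Each row is from 100,000 simulated trials, rejecting when Z < −1.645. The two columns use two common denominators for Z.

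| True curve (17% at 12 months) | k | √E | √((O+E)/2) |
|---|---|---|---|
| Exponential, median 4.7 | 1.00 | 4.2% | 4.9% |
| Weibull, median 6.0 | 1.35 | 6.2% | 7.5% |
| Weibull, Background shape (median 6.3) | 1.45 | 7.6% | 9.2% |
| Weibull, median 6.7 | 1.61 | 11.0% | 13.4% |
| Weibull, median 7.5 | 2.00 | 29% | 34% |
| Weibull, median 8.0 | 2.31 | 54% | 60% |

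The mechanism shows in the mean counts. Under the exponential truth, observed and expected deaths are both 68.1. At median 6.7 months they are 68.9 and 76.8.

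**4. The opposite direction** (√E statistic). If the hazard after 12 months is 1.5 or 2 times as high, the error falls to 0.6% or 0.1%. If 6-month survival is 30% or 35% instead of the 41% implied by the exponential, it is 0.6% or 1.6%. Weibull shapes from 0.7 to 1.1 stay between 4.1% and 4.6%.

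**5. Is length of follow-up the cause?** Cutting the same test at 12 months raises the error from 7.6% to 30% at k = 1.45, and from 11% to 45% at median 6.7 months (√E statistic).

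**6. Effect of a correct null.** With the reference curve given the true Weibull shape, the error returns to 4.0–4.9% in every row. Simulated power for 30% against 17% under proportional hazards is 93–94%. The exponential design simulated the same way gives 92.6–93.5%; 90.3% is its normal approximation.

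**The case against.** Four objections have weight.

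- **The exponential shape appears in the power statement.** The article does not separately say which reference curve the final analysis will use, and an unseen analysis plan may define a better one. This stands, and it limits the point to the only null the protocol states. It does not remove the conflict between that null and the other figures in the document, or the dependence of the 90.3% on it.
- **The Background trial is a different population.** Its figures are for PD-L1-selected patients of any histology, whereas this trial enrols squamous cancer regardless of PD-L1. This stands, so the 7–9% is illustrative. The contrast with the Discussion does not depend on that trial, but it requires reading 6 to 8 months as a median.
- **Wrong shapes do not always inflate.** Correct, as step 4 shows. A reader might infer that any departure raises the error; the calculations do not support that.
- **The endpoint is overall survival, not a 12-month proportion.** Correct. The 12-month rates only parameterise the effect, so the mismatch is no reason to abandon the log-rank test.

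A reader might also blame follow-up to 36 months, or long survivors on chemotherapy. Step 5 contradicts the first for the shapes suggested by the document. On the second, assumed long-survivor shares of 2% or 5% would give about 10–11% or 21–23%, but the document reports no such shares. The Background shape drawn through 17% has fewer alive at 24 months (0.8%) than the exponential null (2.9%).

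**Conclusion.** The point holds in this form: the sample-size arithmetic is right, but the null curve beneath it disagrees with the survival the same article quotes for chemotherapy. Type I error is therefore not controlled in either direction. On the document's own figures inflation is the likelier direction, from about 6% at a 6.0-month median to 13% at 6.7 months, and above 50% at 8 months.

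These sizes assume that 6 to 8 months is a median, a Weibull form, 17% as the true 12-month rate, no drop-out and a reference curve treated as known. The choice of denominator shifts them by about one to six points and does not change the conclusion.

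Since the exponential alternative has a median of 6.9 months (ln 2/0.1003), inside the quoted chemotherapy range, a reader might infer that the 17% itself is wrong. The document does not settle whether the 17%, the shape or the reading of the range is at fault; it shows only that the three do not fit together. The matter should be corrected before analysis, but it does not invalidate the design.

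**What to change.** 1. Keep the one-sample log-rank test. Define its null cumulative hazard from the historical data: a published Kaplan-Meier or piecewise curve if the cited source offers a usable one, otherwise at least a two-parameter curve matching both the 12-month rate and the median.
2. State how the 17% and the 6 to 8 months fit together, and for which population each holds.
3. Recompute the stated power under that null. With 30% against 17% at 12 months and proportional hazards it should change little (step 6), so no extra patients are expected; if reconciliation moves the 17%, the sample size must be revisited.
4. Report Kaplan-Meier 12-month survival against 17% as a supportive analysis that needs no curve shape. It should not replace the primary test: an exact binomial version with 69 patients (success at 18 or more alive, complete 12-month status) has a type I error of 3.7% and power of 79.8%, about 10 points below the stated 90.3%.

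The cost is a wording change in the protocol or analysis plan and a repeated power calculation.

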## Discussion

In the CROSS trial, van Hagen et al. demonstrated that first-line neoadjuvant chemoradiation using carboplatin and paclitaxel is a highly effective regimen for locally advanced ESCC, leading to patients´ overall survival of more than 50 months in single cases (median DOR of 15 months) [3]. This approach is also considered effective as definite chemoradiotherapy for advanced ESCC patients who are not candidates for subsequent surgery [16] and therefore commonly used in Germany. In these patients, second line treatment with paclitaxel is not an option. However, treatment options after chemoradiation with platin derivatives and taxanes for patients with recurrent cancers are limited. Thallinger and coworkers convincingly demonstrated that 2nd line therapy for these patients is un-standardized [4]. Clinical trials focusing on 2nd line chemotherapy for ESCC patients showed frustrating response rates, enhanced toxicity rates and poor overall survival, mostly limited to 6–8 months [4]. Furthermore, majority of ESCC patients are elder persons [17] with significant co-morbidities which in the clinical practice typically renders these patients ineligible for poly-chemotherapy.

To address this issue, the aim of the RAMONA trial is to evaluate a promising new second line therapy option for elderly ESCC patients. Nivolumab as immunotherapeutical agent blocks interaction of PD-1 molecules expressed by tumor-specific T-cells with its ligand PD-L1 on tumor cells, as reviewed in [18]. PD-L1 expression seems to be significantly increased in ESCC with age and is associated with poor prognosis [19]. Pooled analysis of CheckMate 017 and checkmate 057 studies demonstrated, that higher PD-L1 expression levels were associated with greater OS benefit with nivolumab (HR, 0.42; 95% CI, 0.28 to 0.63) in patients with ≥50% PD-L1 expression, but a benefit was still observed in patients with < 1% PD-L1 expression (HR, 0.78; 95% CI, 0.61 to 0.99) [20]. However, here effects seem to more prominent in non-squamous NSCLC. Antonia and colleagues very recently presented new data hinting towards improved ORR in correlation with PDL-1 expression levels upon nivolumab/ipilimumab combination therapy as compared to nivolumab monotherapy (Chicago Multidisciplinary Symposium in Thoracic Oncology, 2016, [11]). Despite further promising results indicating a correlation of good ORR with expression of PD-L1 in lung cancer (PD1 expression ≥1% ORR 57% vs. 28%) [11, 21], the predictive value of PD-1/PD-L1 expression for nivolumab-based therapies is not fully understood in most tumor entities. Therefore, we implemented a translational part into the trial monitoring PD-1/PD-L1 expression rates during the course of treatment.

Checkpoint-inhibitor treatments combine several advantages, which are especially interesting with regard to ESCC treatment approaches. Firstly, promising overall survival has been reported in squamous cell carcinoma patients of different entities, pointing towards a rationale to test efficacy also in ESCC [6, 11, 22–24]. Secondly, antitumor activity of checkpoint inhibitors was shown when used after radiation-based treatments, which is commonly also performed in ESCC treatment. For instance, in a randomized phase III trial including stage II NSCLC patients (i.e. patient that undergo surgery with curative intent), Antonia and coworkers demonstrated that PFS was increased by durvalumab treatment after chemotherapy/radiotherapy compared to chemotherapy/radiotherapy alone [25]. In line, NSCLC patients treated with pembrolizumab showed longer PFS (HR 0.56 [95% CI 0.34–0.91], *p* = 0.019) and increased OS (HR 0.58 [95% CI 0.36–0.94], *p* = 0.026) if they had received any radiotherapy as compared to non-radiated patients [26]. An association of radiotherapy with improved rates of index lesion response in 68% of melanoma patients treated with ipilimumab [27] further underline possible synergistic effects of radiation and immunotherapy on local on distant tumor control as reviewed in [28].

Kudo et al. reported that even for heavily pretreated ESCC patients, immunotherapy with nivolumab alone prolonged overall survival of Asian patients by median 10.8 months (95% CI 7·4–13·3) [9]. Additionally, the risk profile of ESCC patients [1, 29–32] in part overlaps with that of NSCLC patients who are often heavy smokers. In line, available data reveals that especially heavy smokers seem to profit from immunotherapy (Objective response: current and former smokers vs never-smokers (46% [30 of 65] vs 27% [3 of 11]) [11].

ESCC is most frequently diagnosed between 65 and 74 years [17], defining the patient cohort as mostly elderly with per se accumulated co-morbidities, impaired pharmacokinetics and a potentially declined functional reserve [13]. To objectify the functional reserve of the patients and its impact on treatment outcome, a comprehensive geriatric assessment (CGA) is recommended [33]. However, CGA is time consuming and rarely feasible in clinical practice. Thus, we decided to assess the vulnerability of our study subjects by the G8 questionnaire and implement the more complex DAFI assessment only for patients below G8 cut-off (≤14 points). The DAFI is a condensed, validated CGA with 51 items lasting approximately 30 min of which > 80% can be self-reported by the patient [34]. Based on Cohen et al., we estimated that ~ 40% of the patients will belong to a pre-frail group with DAFI indices between 0.2 and 0.35. These patients can enter the RAMONA study upon investigator’s decision as immune-oncological treatments are known to be well-tolerated [11]. Even for combined nivolumab/ipilimumab therapy, grade ≥ 3 toxicities are reported to occur in only 33% in NSCLC [11]. As the CheckMate Trial 214 revealed grade 3 and 4 toxicities in up to 46% of the patients with advanced renal cell carcinoma treated with nivolumab and ipilimumab [35], we consider the RAMONA dosage treatment scheme with longer intervals of ipilimumab administration to provide better tolerability (CheckMate 214 ipilimumab Q3W as compared to Q6W in our study).

However, to ensure that patients are eligible for nivolumab/ipilimumab combination therapy in the RAMONA trial, a safety assessment is performed after a 3 week run-in phase of nivolumab alone. Only those patients with toxicities grade ≤ 2 will be escalated.

Taken together, we used the findings discussed above to formulate the rationale of the RAMONA study and to transfer current knowledge on immunotherapy to the fragile cohort of elderly Caucasian ESCC patients. Overall survival was selected as primary endpoint. In line, impressive long term responses of immunotherapy (at least with pembrolizumab) of up to 50 months (median time to initial response of 4 months (range, 2 to 8 months); median DOR of 15 months (range, 6 to ≥26 months) are reported, even after end of treatment [10]. Treatment adherence is often negatively impacted by quality of life (QoL) deterioration in cancer patients. Therefore, adequate preservation of QoL is an important clinical goal in in elderly patients with recurrent ESCC. Thus, ‘Time to QoL Deterioration’ was included as a key secondary endpoint in this trial.

## Conclusion

In conclusion, RAMONA is the first trial to evaluate checkpoint inhibitor based immunotherapy as a novel treatment opportunity in elderly ESCC patients. Based on a recruitment period of 12 months, first results are expected end of 2019.

### Trial status

RAMONA is an ongoing study. Recruitment commenced in April 2018 and the study is at the moment recruiting patients. For a status update please refer to https://clinicaltrials.gov/ct2/show/NCT03416244.

## Abbreviations

AEs/SAEs: Adverse events, serious adverse events
CGA: Comprehensive geriatric assessments
CI: Confidence interval
CTC: Common toxicity criteria
CTLA-4: Cytotoxic T-lymphocyte-associated Protein 4
DAFI: Deficit accumulation frailty index
DOR: Duration of Response
ECOG: Eastern Cooperative Oncology Group
ESCC: Esophageal squamous cell cancer
HR: Hazard ratio
ORR: Objective response rate
OS: Overall survival
PD-1, PD-L1: Programmed cell death protein 1, Programmed death-ligand 1
PFS: Progression-free survival
QLQ-C30: Quality of life questionnaire C30
QLQ-ELD14: Quality of life questionnaire ELD14
QoL: Quality of life
RECIST: Response Evaluation Criteria In Solid Tumors
